### Data collection and management

2.8

All data collected during the study will be recorded in CRFs. CRFs are kept current to enable the study monitor to review the status of the subjects throughout the course of the study. Data monitoring will be performed by Clinical Research Associate (CRA) of the sponsor. The monitor will review the CRFs and source documents and discuss any missing or spurious data with the investigator. All queries will be resolved in a timely manner by the investigator. The resolution of queries will be recorded in the database. Clean data sets will be provided for statistical analyses and reporting.

The trial schedule is shown in Table 1.

**Table 1 T1:**
[figure not shown]
Trial schedule.

### Sample size

2.9

The sample size was calculated in accordance with the method described by Giordano et al.^[16]^ In their study, the VAS scores for resting pain in the treatment group were significantly decreased from 42.0 ± 24.2 mm to 25.4 ± 19.9 mm (mean ± standard deviation) over 12 weeks. Conversely, the VAS scores for resting pain in the placebo group were increased from 40.9 ± 23.6 mm to 41.0 ± 20.5 mm during the same period. On the basis of these results, we suppose that the change in the treatment group will be –16.6 mm and that in the placebo group will be 0.1 mm. The sample size for this study has been determined using the following parameters:

Superiority testLevel of significance, α = 0.05Two-sided testβ = 0.2, power of test = 80%Ratio of the number of subjects in the test and placebo groups, λ = 1, n_t_ (subject number of the test group) = λn_c_ (subject number of the placebo group)Difference between the groups, Δ = 16.7Standard deviation, *σ* = 27.04 (in both groups)

A sample size of 42 subjects per group was calculated, and on the assumption of a dropout rate of 15%, 50 participants will be recruited into each group.

### Statistical analysis

2.10

Statistical analyses will be computed by using SPSS version 24.0 (SPSS Inc., Chicago, IL). The collected data will be analyzed by using full analysis set analysis, per protocol set analysis, and safety set analysis methods. Missing data will be analyzed by the last observation carried forward method. Baseline characteristics between the test and placebo groups will be evaluated by using the 2-sample *t* test for continuous variables. Categorical variables will be evaluated by using the Chi-square test, Fisher exact test, or McNemar test, and expressed as frequencies and percentages. A paired *t* test will be used to compare the effect within each group both before and after the intervention. ANCOVA and 2 sample *t* tests will be used to compare the net changes between the 2 groups. Skewed variables will be analyzed by using a logarithmic transformation or Wilcoxon rank sum test. Treatment-emergent adverse events (TEAEs) will be coded using the Medical Dictionary for Regulatory Activities (MedDRA) and the percentage of subjects with AEs will be determined and evaluated by using Chi-square test or Fisher exact test. The results will be expressed as the mean ± standard deviation (SD) values and a *P* value of <.05 will be considered to indicate a statistically significant difference.

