### Study design

2.1

This is a 12-week, multicenter, randomized, double-blind, placebo-controlled, parallel-group study. In total, 100 participants will be recruited at Kyung Hee University Korean Medicine Hospital at Gangdong, Kyung Hee University Korean Medicine Hospital, and Dongguk University Bundang Oriental Hospital in Korea. Protocol version is ver.1.4, dated September 06, 2019. Written informed consent will be obtained from each participant before the commencement of any study-related procedure. After written informed consent has been obtained, a screening test will be conducted; subjects meeting all the eligibility criteria will be randomly allocated to either the test group or the control group at a 1:1 ratio. The test group will be instructed to consume the CE extract for 12 weeks and the control group will be instructed to consume the placebo product for 12 weeks. All enrolled subjects will receive guidance on maintaining general diet and activity levels during the study. The participants will visit the hospital four times during the study. Scheduled assessments will be conducted at screening (Week –2 to 0), baseline (Week 0), and at the end of Weeks 6 and 12. The study flow chart is shown in Figure 1.

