#### Primary outcomes

2.7.1

The primary outcomes will be the VAS score, the Korean-Western Ontario and McMaster Universities (K-WOMAC) index, and the Korean-Short Form Health Survey 36 (KSF-36) score.

VAS will be used to measure changes in joint pain at 6 and 12 weeks after treatment administration and compare it with the baseline score.The K-WOMAC index will be used to measure changes in joint pain and function at 6 and 12 weeks after treatment administration and compare it with the baseline index.The KSF-36 score will be used to measure changes in physical and mental functions at 6 and 12 weeks after treatment administration and compare it with the baseline score.

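### Last observation carried forward is the only missing-data method; at the planned 15% dropout it shrinks the expected 12-week VAS difference modestly, and with unequal dropout it can bias it in either direction

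*Protocol article*

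**What the plan says.** The Statistical analysis section states: "Missing data will be analyzed by the last observation carried forward method". It does not restrict this to any outcome or analysis set, and it names no second method and no sensitivity analysis under a different assumption. On analysis sets it says: "The collected data will be analyzed by using full analysis set analysis, per protocol set analysis, and safety set analysis methods". The completed data then go into standard comparisons: "ANCOVA and 2 sample *t* tests will be used to compare the net changes between the 2 groups".

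The Study design section places assessments at screening, at baseline "and at the end of Weeks 6 and 12". Under Primary outcomes, "VAS will be used to measure changes in joint pain at 6 and 12 weeks after treatment administration", each compared with baseline; K-WOMAC and KSF-36 follow the same schedule. Under Secondary outcomes, ESR and CRP are defined only as Week 12 against baseline.

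The Sample size section states: "we suppose that the change in the treatment group will be –16.6 mm and that in the placebo group will be 0.1 mm". It adds, "on the assumption of a dropout rate of 15%, 50 participants will be recruited into each group".

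**The concern.** LOCF gives the correct Week 12 mean only if people who leave would, on average, not have changed after their last visit. With one visit between baseline and the end, the value carried forward is either pre-treatment or six weeks old. The sample-size reasoning supposes a substantial change over 12 weeks on treatment and almost none on placebo, so holding dropouts at an earlier value pulls the treated mean toward no change.

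The bias need not always be toward no effect. If both arms improve, as can happen in a pain trial, the arm that loses more participants is held nearer to baseline and looks worse. The section on withdrawal and dropout lists adverse events and interfering medicines or treatments as reasons for withdrawal, and both could differ by arm. At stake is the accuracy of the main effect estimate and, with unequal dropout, some of the error control.

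**Working it through.** **Inputs from the Sample size section.** Difference 16.7 mm (−16.6 on treatment, +0.1 on placebo), SD 27.04 in both groups, two-sided α = 0.05, power 80%, dropout 15%, 50 recruited per group.

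**The plan's own figure.** n = 2 × [27.04 × (1.960 + 0.842) / 16.7]² = 41.15, so 42 per group. Then 42 / 0.85 = 49.4, so 50. Both stated numbers are reproduced. Expected dropouts are 0.15 × 50 = 7.5 per arm.

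**1. Dilution with equal dropout.** Let q be the dropout share and c the average fraction of the final effect present in the carried value. The expected LOCF difference is 16.7 × (1 − q + q × c). The target is the Week 12 effect if dropouts would have followed the same average course as those who stay. The protocol gives neither the timing of dropout nor the Week 6 effect, so both are assumptions. With q = 0.15:

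| Dropout timing | Share of effect at Week 6 | c | Expected difference |
|---|---|---|---|
| All before Week 6 | not used | 0 | 16.7 × 0.85 = 14.2 mm |
| Half before, half after | 0.5 | 0.25 | 16.7 × 0.8875 = 14.8 mm |
| All after Week 6 | 0.5 | 0.5 | 16.7 × 0.925 = 15.4 mm |
| All after Week 6 | 0.75 | 0.75 | 16.7 × 0.9625 = 16.1 mm |

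The second row is a loss of 1.9 mm, or 11%. Over the table the loss is 0.6 to 2.5 mm. It would vanish only if every dropout left after Week 6 with the full effect already present.

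**2. Power.** Take the first row. The variance per arm is (1 − q)σ² + q(1 − q)m², where m is the arm's mean change.
- Treatment: 0.85 × 27.04² + 0.1275 × 16.6² = 656.6 (SD 25.62).
- Placebo: 621.5 (SD 24.93).
- LOCF: SE = √[(656.6 + 621.5) / 50] = 5.06 mm; power = Φ(14.195 / 5.06 − 1.96) = 80.2%.
- Expected completers (42.5 per arm): SE = 27.04 × √(2 / 42.5) = 5.87 mm; power = Φ(16.7 / 5.87 − 1.96) = 81.2%.

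Effect and standard error shrink together, so power barely moves.

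**3. Type I error with equal dropout.** A simulation used 50 per arm, 15% dropout in both arms and half of it before Week 6. Assumed SDs were 24, 20.2 and 20.2 mm at the three visits, and assumed correlations 0.35, 0.3 and 0.6. It gave a type I error of 4.9% with no change in either arm and 4.8% with a common 16 mm improvement. The mean LOCF standard error matched the true spread of the estimate: 5.03 against 5.04 mm, and 5.11 against 5.14 mm.

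**4. Unequal dropout, no true difference.** Assume 22% dropout in one arm and 8% in the other, half before Week 6, half the change present at Week 6, and a common improvement m. A dropout then misses on average 0.5 × 1 + 0.5 × 0.5 = 0.75 of m. The spurious difference is (0.22 − 0.08) × 0.75 × m = 0.105 × m.
- m = 12 mm: 1.3 mm.
- m = 20 mm: 2.1 mm.

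Simulated type I error over these cases is about 5.5–7%, rising to 8.0% in some runs with other assumed visit correlations (0.3–0.6). Swapping which arm loses more reverses the sign.

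**5. ESR and CRP.** The only earlier scheduled value in the text is baseline. If it is carried forward and no sample is taken at withdrawal, dropouts score zero change, and at 15% dropout any true difference is multiplied by 1 − 0.15 = 0.85.

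**The case against.** The strongest reply is that the effect is small and, on the plan's own assumptions, goes against the product. That largely stands. With equal dropout the loss is 0.6–2.5 mm of 16.7 mm, power is about the same and the 5% level holds. Inflation needs both unequal dropout and a common improvement, and the protocol states neither: it assumes one dropout rate and a placebo change of +0.1 mm. With +0.1 mm in both arms, the 22%/8% split gives a shift of only 0.105 × 0.1 = 0.01 mm, and simulated type I error was 4.9%.

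A reader might infer more than the documents support:

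- *That treating imputed values as observed makes the standard error about 8% too small and so breaks the 5% level.* It does not. The LOCF standard error is smaller than a completers' one because the LOCF estimate varies less; step 3 shows that it matches the true spread.
- *That the plan itself expects the effect to build steadily to Week 12.* Only baseline and 12-week values are given. An effect largely reached by Week 6 would cost little in later dropouts.
- *That every dropout will have exactly zero change in ESR and CRP.* The trial schedule (Table 1) is not shown, so a withdrawal sample cannot be excluded; and if baseline may not be carried, the values stay missing.

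The article also does not define its full analysis set. If that set requires a post-baseline value, early dropouts are excluded and only the Week 6 carry-forward matters. The per-protocol analysis means that the LOCF result will not stand alone, but it addresses a different population and does not test the missing-data assumption.

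The details of a model can be left to a statistical analysis plan. The choice of LOCF was not left open: the article makes it.

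**Conclusion.** The point holds as a should-fix. Following the stated method with visits at Weeks 0, 6 and 12 gives a biased Week 12 estimate unless outcomes are flat after dropout. The central figure is about 14.8 mm in place of 16.7 mm, with a range of 14.2–16.1 mm over the dropout timings and Week 6 effects considered. It rests on 15% dropout in each arm and on dropouts otherwise following the same average course as completers. The harm is a distorted estimate, not lost power, and with equal dropout there is no loss of error control.

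The direction is not guaranteed to be conservative: unequal dropout combined with improvement in both arms can favour either arm, by about 1.3–2.1 mm in the assumed scenario. The ESR and CRP attenuation to about 0.85 is conditional on baseline being carried and no withdrawal sample being taken.

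**What to change.** For the Week 12 contrast of VAS, K-WOMAC and KSF-36, replace LOCF as the main method with a likelihood-based mixed model for repeated measures. Fit it to the observed Week 6 and Week 12 values, adjusted for baseline, with treatment, visit and their interaction. For ESR and CRP, use a baseline-adjusted analysis of observed cases, or multiple imputation. Keep LOCF at most as a sensitivity analysis, and add one analysis that allows for data not missing at random, for example imputing dropouts from the placebo pattern. Make the change before unblinding.

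The cost is revised wording and a little more programming; no new data are needed. The main analysis would then rely on a missing-at-random assumption that the data cannot confirm, which is why the additional sensitivity analysis belongs beside it.

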### Randomization and blinding

2.4

The randomization sequence will be generated by Jaseng Spine and Joint Research Institute of Jaseng Medical Foundation, and Microsoft Excel 2010 (Microsoft Inc., USA) will be used to create a blocked randomization list. Randomization codes will be provided in envelopes and kept at each center; randomization will be performed at each center. Eligible participants will be randomly assigned to either the test group or the placebo group in a 1:1 ratio. This study design is double-blind; therefore, both the investigators and the subjects will be blinded during the study. To maintain the blinding, the appearance of the test and placebo product will be identical. The study blind will be broken in situations such as SAEs.

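### Two different tests are assigned to the same between-group comparison, and nothing says which one decides

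*Protocol article*

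**What the plan says.** Section 2.10 (Statistical analysis) gives the between-group method in one sentence: "ANCOVA and 2 sample *t* tests will be used to compare the net changes between the 2 groups". The two methods are joined by a plain conjunction. No order is given, and there is no rule for when each applies. The section closes with a single threshold for all tests: "a *P* value of <.05 will be considered to indicate a statistically significant difference". It also provides that "Skewed variables will be analyzed by using a logarithmic transformation or Wilcoxon rank sum test".

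Section 2.9 (Sample size) plans on a VAS difference of 16.7 mm between the groups' changes, with the SD given as "27.04 (in both groups", two-sided α of 0.05 and "power of test = 80"%. The cited study's treatment arm "decreased from 42.0 ± 24.2 mm to 25.4 ± 19.9 mm" and its placebo arm "increased from 40.9 ± 23.6 mm to 41.0 ± 20.5 mm". The result is 42 per group, raised to 50 for 15% dropout.

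Section 2.4 (Randomization and blinding) describes a blocked list and says that "randomization will be performed at each center". Section 2.3.1 admits subjects with VAS above 30 mm.

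**The concern.** A t test on change fixes the weight given to baseline at exactly one. ANCOVA adjusted for baseline estimates that weight from the data. When the correlation between baseline and follow-up is modest, the two can give clearly different estimates and P values. If both are run and neither has been named as decisive, the reader of the results cannot tell whether the reported one was chosen after the data were seen.

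Two things are at stake. One is the error rate, if either significant result is allowed to count. The other is precision, if the change-score t test ends up as the headline: subtracting a baseline that is only weakly related to follow-up adds noise.

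**Working it through.** **Inputs.** From section 2.9: Δ = 16.7 mm, σ = 27.04 mm, two-sided α = 0.05, power 80%, dropout 15%, and the cited study's baseline and 12-week SDs (24.2 and 19.9 treatment; 23.6 and 20.5 placebo). From section 2.3.1: entry VAS above 30 mm.

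**The plan's own figure.** n per group = 2σ²(1.960 + 0.842)²/Δ² = 41.15, rounded up to 42. Then 42/0.85 = 49.4, rounded up to 50. Both stated figures reproduce. They are for an unadjusted comparison of changes, whose exact t-test power at 42 per group is 79.9%.

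**Implied correlation.** If 27.04 is the SD of change, r = (SD₀² + SD₁₂² − 27.04²)/(2·SD₀·SD₁₂).
- Treatment: (24.2² + 19.9² − 27.04²)/(2 × 24.2 × 19.9) = 0.260.
- Placebo: (23.6² + 20.5² − 27.04²)/(2 × 23.6 × 20.5) = 0.254.
- Pooled SDs 23.90 and 20.20: r = 0.257.

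**Precision on the cited study's SDs.** ANCOVA residual SD = SD₁₂√(1 − r²) = 20.20 × √(1 − 0.257²) = 19.52 mm, against 27.04 mm for change. Variance ratio = (27.04/19.52)² = 1.92. At 42 per arm the 95% CI half-width is 8.5 mm against 11.7 mm, and power is 97.2% against 79.9%.

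**Precision with the entry rule (assumption).** Take baseline as normal with mean 41.45 mm (the average of 42.0 and 40.9) and SD 23.90, cut to 30–100 mm, with the regression of follow-up on baseline unchanged. About 32% of that distribution lies below 30 mm. The baseline SD falls to 15.68 mm. With slope β = r × 20.20/23.90 = 0.217, the SD of change = √[(1 − 0.217)² × 15.68² + 19.52²] = 23.06 mm. Variance ratio = (23.06/19.52)² = 1.40.

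**Type I error if either test counts.** Under no effect, the two test statistics correlate at (ANCOVA SD)/(change SD). At r = 0.257 this is 19.52/27.04 = 0.722. The bivariate normal probability that at least one exceeds ±1.96 is then 8.2%. A simulation with 42 per arm (20,000 runs) gave 7.9%, with each test alone at 4.9% and 4.8%.

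| Setting | r | Variance ratio, change : ANCOVA | Power at 42/arm, t test v ANCOVA | Either-test type I error |
|---|---|---|---|---|
| Cited study's SDs | 0.257 | 1.92 | 80% v 97% | 8.2% |
| Cited study's SDs | 0.5 | 1.62 | 92% v 99% | 7.9% |
| Cited study's SDs | 0.7 | 1.46 | 99% v >99% | 7.6% |
| Baseline cut at 30 mm | 0.257 | 1.40 | 91% v 97% | 7.5% |
| Baseline cut at 30 mm | 0.5 | 1.27 | 97% v 99% | 7.1% |
| Baseline cut at 30 mm | 0.7 | 1.20 | >99% v >99% | 6.9% |

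The r column is the correlation before the cut. All figures are for one outcome at one time point in one analysis set.

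**The case against.** The best defence is that this is a condensed article and the analysis plan is not shown. Covariates and the lead analysis set are commonly left to that plan, so their absence here is not an error. That stands. It does not cover the choice of test, because section 2.10 does not defer that choice: it states that both tests will be used.

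The defence is also right that ANCOVA is planned and named first, so precision is lost only if the t test is made the headline. No sentence says that either significant result would suffice, so the 7–8% is conditional. The implied correlation is back-solved from an SD whose derivation section 2.9 does not give.

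A reader might infer several stronger points that the document does not support:
- **The ANCOVA ignores baseline and centre.** The text does not name the covariates. ANCOVA by definition has at least one, and baseline is the likely choice.
- **Randomization was stratified by centre and the analysis overlooks it.** Section 2.4 has a blocked list with codes held and used at each centre. It does not say that each centre has its own list. The gain from a centre term cannot be computed, because no between-centre variance is given.
- **A log transform would be applied to negative changes.** The sentence concerns skewed variables, and CRP and ESR (section 2.7.2) are natural targets.
- **Wilcoxon is a third free choice that pushes the error rate higher still.** The text ties it to skewed variables.
- **The trial is underpowered, or its 80% is wrong.** The 42 per group was calculated for the unadjusted comparison and reproduces.

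**Conclusion.** The point holds in a limited form. Section 2.10 commits to two different tests for one comparison, with P<.05 as the criterion and no statement of which decides. Nothing elsewhere in the article settles it.

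If either result could count, the type I error for a single outcome and time point is about 7–8%. If the t test led, the variance would be about 1.9 times that of baseline-adjusted ANCOVA on the cited study's SDs. Given this trial's entry rule, 1.2–1.4 is the more relevant range, and it rests on normal truncation and an unchanged regression on baseline. The 97% against 80% power contrast should therefore not be read as what this trial would see. At the implied correlation, about 97% against 91% fits the entry rule better. The loss is one of efficiency: the t test still has adequate power for 16.7 mm.

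**What to change.** In section 2.10, name one deciding between-group analysis: ANCOVA of the Week-12 change on treatment, adjusted for the baseline value, reported as the adjusted difference with its 95% CI. Add centre as a term if the randomization lists are separate by centre, and state whether they are. Label the 2-sample t test and any Wilcoxon result as sensitivity analyses that do not decide the conclusion.

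This should be done before unblinding, in the protocol or in the analysis plan if that is where the choice is recorded. The cost is wording only, because baseline scores and centre are already recorded. The sample size need not change.

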**Discussion:**

This clinical trial is expected to provide evidence of the efficacy and safety of CE extract as a treatment for mild OA.

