*E ulmoides* Oliver, a member of the Eucommiaceae family, is a traditional herbal medicine in China. It has been used to treat various diseases in Korea, Japan, and China.^[6]^ Various parts of *E ulmoides*, such as the bark, leaf, stem, and flower, have traditionally been used to treat diseases. In addition, *E ulmoides* is nontoxic and has been reported to have few side effects.^[7]^ Previous studies have reported various biological activities of *E ulmoides*, such as antihypertensive, anti-inflammatory, anti-obesity, antitumor, and cardiovascular-protective.^[8–11]^*E ulmoides* has traditionally been used in China to treat back, ankle, and knee pain; in particular, the bark of *E ulmoides* has been used to cure arthritis.^[6,12]^ Recent studies have reported the effectiveness of *E ulmoides* against chronic inflammatory diseases such as OA. Kim et al demonstrated the anti-inflammatory effects of CE, showing inhibition of tumor necrosis factor-α (TNF-α) and interleukin-6 (IL-6) in lipopolysaccharide (LPS)-stimulated mouse macrophages.^[13]^ Koh et al^[14]^ conducted an in vitro study that showed the anti-inflammatory effects of CE in RAW 264.7 cells. CE suppressed inflammatory mediators, such as inducible nitric oxide synthase (iNOS), COX-2, TNF-α, and interleukin-1β (IL-1β), and also modulated the toll-like receptor 4 (TLR-4) pathways, which are expressed in the cartilage of patients with OA.^[14,21]^ The potential of CE as a medicine for chronic inflammatory disease has also been demonstrated. Li et al^[15]^ found the collagen synthesis-promoting effects of CE in an in vivo study. Lu et al^[12]^ demonstrated that elevated serum levels of matrix metalloproteinases (MMPs) are associated with cartilage degradation.^[22]^ The levels of MMP-1, MMP-3, and MMP-13 in the serum decreased in the CE-treated group in the study of Lu et al.^[12]^ Park et al conducted a prospective, randomized, double-blind, multicenter comparative clinical trial to evaluate the efficacy and safety of GCSB-5 compared with those of celecoxib.^[23]^ GCSB-5 is a mixture of 6 herbs and *E ulmoides* Oliver is one of its main components. Patients with knee OA were enrolled and randomly assigned to the GCSB-5 group or the celecoxib group for 12 weeks. The occurrence of AEs or adverse drug reactions was not significantly different between the 2 groups. The total WOMAC and VAS scores improved in both groups. The authors proved the therapeutic effect of GCSB-5 against OA. Therefore, for this clinical trial, we hypothesized that CE may slow down or prevent OA.

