
This trial has some limitations. First, the subjects may be exclusively Korean. Therefore, the data from this clinical trial cannot be applied to other ethnic groups. Second, owing to the small sample size, the results of this study cannot be generalized. However, few clinical trials have been conducted on the effects of CE on OA. Therefore, despite these limitations, this trial is expected to demonstrate the efficacy and safety of CE for the treatment of patients with mild OA. Furthermore, the results of the study will serve as a foundation for the development of CE as a dietary supplement.

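### With about 50 subjects per arm, a non-significant chi-square or Fisher test on adverse events cannot support the expectation that the trial will demonstrate safety

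*Protocol article*

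**What the plan says.** Section 2.10 (Statistical analysis) of the protocol article has treatment-emergent adverse events (TEAEs) coded in MedDRA and then states that "the percentage of subjects with AEs will be determined and evaluated by using Chi-square test or Fisher exact test". The same section sets one criterion for all tests: a P "value of <.05 will be considered to indicate a statistically significant difference". It gives no interval, margin or expected rate for AEs, and it names a safety set without further detail.

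Section 2.9 (Sample size) derives the trial's size from a difference in VAS pain only: "A sample size of 42 subjects per group was calculated, and on the assumption of a dropout rate of 15%, 50 participants will be recruited" per arm. Allocation is 1:1 (Section 2.1).

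Section 2.7.3 (Safety outcomes) lists AEs, laboratory tests, vital signs, weight and electrocardiography, and has severity and relation to the product recorded for each AE.

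Section 3 (Discussion) ends with the expectation that "this trial is expected to demonstrate the efficacy and safety of CE for the treatment of patients with mild OA". The Abstract is milder: the trial is "expected to provide evidence of the efficacy and safety of CE extract as a treatment for mild OA".

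**The concern.** The stated AE comparison is a test of the hypothesis of no difference. Such a test can signal harm when it rejects. When it does not reject, it says little unless the study was large enough to find a harm that matters. This study was sized for a pain score, not for AEs. The Discussion nevertheless expects safety to be demonstrated and presents the trial as groundwork for developing the Cortex Eucommiae (CE) extract as a dietary supplement.

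If the AE table shows only percentages and a P value above .05, nothing in the stated analysis tells the reader how large an excess of AEs remains compatible with the data. A lack of evidence of harm could then pass for evidence of safety.

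**Working it through.** **Inputs from the document.** 50 recruited per arm and 42 after dropout, VAS difference 16.7 mm, SD 27.04 mm, two-sided alpha 0.05, power 80% (all Section 2.9); chi-square or Fisher test at P < .05 (Section 2.10).

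**Assumptions.** Placebo AE rates of 5% to 40%, because the document gives none; the rate doubled on CE; the AE test two-sided, as in Section 2.9; chi-square without continuity correction.

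**1. The plan's own figure.** n = 2 × [27.04 × (1.960 + 0.842) / 16.7]² = 41.15, rounded up to 42 per group. Then 42 / 0.85 = 49.4, rounded up to 50. The stated size reproduces, and it concerns VAS only.

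**2. Power of the AE test for a doubling.** For each pair of rates, power is the sum over all counts a and b of Bin(a; n, p_placebo) × Bin(b; n, p_CE), taken where the test gives P < .05.

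| Placebo vs CE | Chi-square, n = 50 | Fisher, n = 50 | Chi-square, n = 42 | Fisher, n = 42 |
|---|---|---|---|---|
| 5% vs 10% | 15% | 6% | 15% | 5% |
| 10% vs 20% | 30% | 20% | 26% | 18% |
| 15% vs 30% | 44% | 35% | 39% | 30% |
| 20% vs 40% | 60% | 52% | 52% | 44% |
| 25% vs 50% | 75% | 68% | 68% | 60% |
| 30% vs 60% | 88% | 83% | 83% | 76% |
| 40% vs 80% | 99% | 98% | 98% | 96% |

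With 50 per arm, power for a doubling passes one half at a placebo rate of about 17% for chi-square (47% power at a rate of 16%, 50% at 17%) and about 20% for Fisher (48% at 19%, 52% at 20%). The columns for 42 are a pessimistic bound, because subjects dosed before dropping out still contribute AE data.

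**3. Size needed for 80% power** (normal approximation, no continuity correction): 435 per arm for 5% vs 10%, 199 for 10% vs 20%, 82 for 20% vs 40%, and 42 for 30% vs 60%.

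**4. What an interval would show.** Suppose 10 of 50 on CE and 5 of 50 on placebo have an AE. Fisher gives P = 0.26. The risk difference is 20% − 10% = 10 percentage points, with a Newcombe 95% confidence interval of −4 to +24 points. The P value alone hides that an excess of more than 20 points is still compatible with the data.

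**5. A bound that needs no assumed rate.** If an event is seen in none of 50 CE subjects, the one-sided 95% upper limit p solves (1 − p)^50 = 0.05, so p = 1 − 0.05^(1/50) = 5.8%.

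**The case against.** The strongest reply is that the document contains no rule by which safety would be declared from a non-significant P value. That is correct. A reader might infer that safety is to be judged by this test, but Section 2.10 also reports percentages, and Section 2.7.3 adds laboratory, vital-sign, weight and ECG data with severity and causality. The sentence in the Discussion is an expectation, not a decision rule. What remains is that no stated analysis at this size supports the verb *demonstrate*.

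A second reply concerns power. A reader might infer that the test would usually miss a doubling of risk whatever the rate. The table does not support that: at 20% vs 40% the test detects the difference slightly more often than not, and at 30% vs 60% power exceeds 80%. The endpoint counts subjects with any AE, so a low overall rate cannot be presumed. The statement holds only below the rates given above, a range that would cover a low overall rate and the less frequent individual event types.

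Three other inferences are also too strong:

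- The Discussion says of the earlier herbal-mixture trial that "The occurrence of AEs or adverse drug reactions was not significantly different between the 2 groups". This might be read as the authors already taking non-significance for safety, but the conclusion they draw there is about therapeutic effect.
- The admitted small sample might seem to contradict the safety expectation. The text uses it to limit generalizability, which is a different matter, and discloses it as a limitation.
- Section 2.10 codes TEAEs but then speaks of AEs. This might be read as counting events before the first dose. Shorthand is the more natural reading, and onset windows are usually defined in the full protocol or analysis plan.

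Finally, an interval may be specified in an analysis plan that is not shown. Its absence from an article is therefore not the fault here. The point is that the article fixes a test and states an expectation that the test cannot meet.

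**Conclusion.** The point holds in a limited form. The only between-group AE comparison stated is a test of no difference, in a trial sized for VAS alone, and a non-significant result from it would not be evidence of safety.

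How weak the test is depends on a placebo AE rate that the document does not give. For a doubling, power at 50 per arm runs from 6% (Fisher) or 15% (chi-square) at a 5% placebo rate to 98% or 99% at a 40% rate. The zero-event limit of 5.8% rests on no assumed rate and is enough to show that about 50 exposed subjects over 12 weeks can describe tolerability but cannot establish safety.

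This is an inexpensive improvement to the reporting and wording. It does not affect the efficacy analysis or the data collected.

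**What to change.** **Section 2.10.** As the main AE comparison, report for each arm the proportion of safety-set subjects with at least one TEAE, with the between-group risk difference and its 95% confidence interval. The chi-square or Fisher P value may stay as a descriptive figure. Add a sentence saying that P ≥ .05 will not be interpreted as evidence of safety.

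**Section 3, Discussion.** Reword the closing expectation so that, for safety, the trial describes 12-week safety and tolerability in about 50 subjects exposed to CE. It would help to add that an event not seen in 50 subjects could still have a risk of up to about 6%. The Abstract's milder wording needs no change.

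**Cost.** A few sentences and one extra column in the AE table, with no new data or subjects. The downside is a more modest safety claim.
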